## Abstract

**Background:**

Depression is a common and distressing mental health problem that is responsible for significant individual disability and cost to society. Medication and psychological therapies are effective for treating depression and maintenance anti-depressants (m-ADM) can prevent relapse. However, individuals with depression often express a wish for psychological help that can help them recover from depression in the long-term. We need to develop psychological therapies that prevent depressive relapse/recurrence. A recently developed treatment, Mindfulness-based Cognitive Therapy (MBCT, see http://www.mbct.co.uk) shows potential as a brief group programme for people with recurring depression. In two studies it has been shown to halve the rates of depression recurring compared to usual care.

This trial asks the policy research question, is MBCT superior to m-ADM in terms of: a primary outcome of preventing depressive relapse/recurrence over 24 months; and, secondary outcomes of (a) depression free days, (b) residual depressive symptoms, (c) antidepressant (ADM) usage, (d) psychiatric and medical co-morbidity, (e) quality of life, and (f) cost effectiveness? An explanatory research question asks is an increase in mindfulness skills the key mechanism of change?

**Methods/Design:**

The design is a single blind, parallel RCT examining MBCT vs. m-ADM with an embedded process study. To answer the main policy research question the proposed trial compares MBCT plus ADM-tapering with m-ADM for patients with recurrent depression. Four hundred and twenty patients with recurrent major depressive disorder in full or partial remission will be recruited through primary care. Depressive relapse/recurrence over two years is the primary outcome variable. The explanatory question will be addressed in two mutually informative ways: quantitative measurement of potential mediating variables pre/post-treatment and a qualitative study of service users' views and experiences.

**Discussion:**

If the results of our exploratory trial are extended to this definitive trial, MBCT will be established as an alternative approach to maintenance anti-depressants for people with a history of recurrent depression. The process studies will provide evidence about the effective components which can be used to improve MBCT and inform theory as well as other therapeutic approaches.

**Trial registration number:**

ISRCTN26666654

## Background

Depression is a major public health problem that, like other chronic conditions, tends to run a relapsing and recurrent course [1], producing substantial decrements in health and well-being [2]. WHO predicts that by 2020 depression will be the second leading cause of disability in the world [3]. The current cost of mood disorders in the UK has been calculated at 1.5% of GDP [4] and a recent King's Fund report projects that the cost will be £12.15 billion by 2026 [5]. More than 50% of patients experience at least 2 episodes of depression. Moreover, without ongoing treatment people suffering recurrent depression suffer relapse/recurrence at rates as high as 80%, even after successful acute treatment [6,7]. Thus, most of the prevalence, burden and cost of depression is a consequence of relapse/recurrence and the majority of the burden attributable to depression could be offset through interventions aimed at the prevention of depressive relapse/recurrence [8]. Currently the majority of depression is treated in primary care, and m-ADM is the mainstay approach to preventing relapse/recurrence [9-11]. To stay well NICE recommends that people with a history of recurrent depression continue m-ADM for at least two years [11]. However, many patients experience unpleasant side-effects, rates of ADM adherence tend to be low, and many patients express a preference for psychosocial interventions [12-14]. Service user organisations therefore advocate greater availability of psychosocial therapies. Similarly, the King's Fund recommends: "expansion of evidence-based interventions in primary care" and "more research into the cost-effectiveness of a range of interventions, including mental health promotion and prevention initiatives" [[5]; p. xxi]. In line with this, significant government initiatives such as the Improving Access to Psychological Therapies programme are beginning to explore accessible, acceptable and cost-effective psychosocial models of care and envisage up to 250 centres offering psychosocial treatments within a decade [4].

### Psychosocial approaches to prevent depressive relapse/recurrence

While there is a strong evidence base for psychosocial treatment of current depression, only more recently has attention turned to preventing depressive relapse/recurrence. Policy initiatives, user group and professional consensus recommend as priorities for future research the development of psychosocial interventions to prevent depressive relapse/recurrence and the use of non-traditional delivery systems, such as group interventions, to maximise accessibility and cost-effectiveness [15,16]. MBCT is a psychosocial group-based relapse prevention programme. It was developed from translational research into mechanisms of depressive relapse/recurrence [17]. There is much clinical enthusiasm for MBCT, as evidenced by high rates of patient engagement and the recent establishment of MBCT therapist training programmes in the UK at the Universities of Bangor, Exeter and Oxford. In summary, MBCT shows the potential to contribute significantly to reducing the prevalence of depression in UK primary care settings.

### Secondary research findings

Narrative reviews of the broad class of mindfulness-based approaches suggest that they produce substantial improvements on measures of depressive symptoms compared with control groups: Cohen's d (or standardised mean difference) = .86, SD = .3 [18]; Cohen's d = .54, 95% CI .39-.68 [19]. Two uncontrolled trials of patients with a history of recurrent depression and high levels of residual symptoms demonstrate improvements in depressive symptoms, with many people in remission at follow up [20,21]. The two most significant well controlled MBCT randomised controlled trials to date found that MBCT plus usual care halved rates of relapse compared to usual care alone, over sixty weeks of follow-up [22,23]. However, both trials excluded people receiving the current treatment of choice (m-ADM), did not compare MBCT with another active treatment, were not based in real world healthcare settings, had relatively short follow-ups, and did not speak to MBCT's mechanism of change. A recent systematic review of the few existing MBCT controlled trials for depression (including these 2 randomised controlled trials) suggests a significant additive effect of MBCT over usual care for patients with recurrent depression, but only for patients who have experienced three or more previous episodes [24]. However, the authors of this review found no trials comparing MBCT with an active treatment, and suggest this as the next step. Moreover, they found no evidence of the "specific effectiveness of MBCT, despite this being the logical progression from the current research." That is to say, no trials speak to whether MBCT works through its specific hypothesised mechanisms and/or through non-specific cognitive-behavioural, psycho-education and group/therapist support components. They suggest "the need for randomised controlled trials to compare MBCT with other non-pharmacological approaches" and that include tests of the specific and non-specific mechanisms of change [24]. A key issue that the current literature leaves unresolved is whether the robustly demonstrated relapse prevention effects of MBCT are due to the hypothesized mechanism of change, the cultivation of mindfulness skills.

### Our exploratory trial

In our exploratory trial 123 patients with recurrent depression on m-ADM were randomised to either continued m-ADM or MBCT plus m-ADM tapering/discontinuation [25]. The findings suggest that MBCT may not only provide an alternative to m-ADM (relapses at 15 months: MBCT 47% *vs*. m-ADM 60%), but that in an adequately powered definitive phase III trial it may produce superior outcomes. The study suggested that MBCT was also superior to m-ADM in terms of improved quality of life, reduced residual depressive symptoms, and reduced psychiatric co-morbidity. Finally, a secondary qualitative study suggested several putative mechanisms of action [26].

### Why is this trial needed now?

First, we have sufficient evidence from existing trials and our exploratory trial to progress to the next stage of the treatment development process: a definitive randomised controlled trial. That is to say, there is preliminary evidence suggesting that MBCT has potential to significantly reduce the prevalence of depression and to do so cost-effectively. Second, in the UK the vast majority of depression presents in primary care, yet the studies reviewed above do not speak to the generalisability of MBCT to real world primary care settings. Third, the randomised controlled trials to date [22,23] were conducted by the group that developed MBCT and an independent replication is needed. Fourth, depression relapse prevention trials are needed that use a more sophisticated and patient-centered approach to outcome assessment that extends beyond 1-year follow-up and assesses patient-centred secondary outcomes [27]. Fifth, none of the research to date speaks to whether MBCT is efficacious through its hypothesised mechanism of action. Such mechanisms research informs theory and treatment and may produce a simpler and more cost-effective approach to relapse prevention. Finally, the ISRCTN Register (June, 2008) records no comparable recent or ongoing trials in the UK. No current trials of recurrent depression speak to mechanisms of change.

## Methods/Design

### Design

The design is a single blind, parallel RCT examining MBCT vs. m-ADM with an embedded process study. To answer the main policy research question: "Is MBCT superior to maintenance antidepressant medication (m-ADM) in preventing depression over 24 months?" the proposed trial compares MBCT plus ADM-tapering with m-ADM for patients with recurrent depression. Depressive relapse/recurrence over two years is the primary outcome variable.

The trial will answer the explanatory question "Is an increase in mindfulness skills the key mechanism of change?" in two mutually informative ways: quantitative measurement of potential mediating variables pre/post-treatment [28] and an embedded qualitative study to elicit service users' experiences of treatment.

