### Interventions

#### Maintenance antidepressants (m-ADM)

As part of the inclusion criteria, patients eligible to take part must be receiving treatment with antidepressant medication in line with the BNF and 2009 NICE guidelines. The m-ADM relapse/recurrence prevention intervention will be an extension of the ADM treatment that is an inclusion criterion for the study. In the UK almost all ADM prescriptions are issued by GPs [32]. Therefore GPs will be responsible for patients' ADM treatment in line with NICE guidelines and contemporary best practice [11]. NICE recommends that patients be maintained on ADM for 2 years after achieving remission, and then should only be tapered in accordance with the NICE guidance for recurrent depression. The guideline recommends that factors such as age, co-morbidity and other risk factors should inform the use of longer-term m-ADM. In the exploratory trial, at study entry the mean time on m-ADM was 340 days, with a significant distribution of patients who had been taking m-ADM for many years. The NICE guidance also speaks to monitoring, ADM type, dose, switching and augmentation.

Medication adherence will be monitored through patients' self-report using the Adult Service Use Schedule (AD-SUS) [33] and the Morisky Medication Adherence Instrument [34] and through manual checks of the GP practice databases at 12 and 24 month follow-ups. We will encourage patients to adhere to medication for the full length of the trial by writing to both the patient and their GP explaining that they have been randomised to maintenance antidepressants and asking them to continue to take a therapeutic level of antidepressants for the 2-year duration of the trial.

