#### (ii) The explanatory questions

These will be examined using a mix of three mutually informative methods:

(a) For the MBCT arm time to relapse/recurrence of depression will be compared using Cox regression proportional hazard survival analysis, allowing for the stratification variables and any group differences in ADM tapering/usage (if rates of tapering/usage are different across the two arms).

(b) Mediational analyses will investigate hypothesised mechanisms of change pre-/post-treatment across the trial arms using approaches to testing mediation that allow multiple mediators in one model using the approach set out by Kraemer et al. (2002) and as used in our exploratory trial [49].

(c) Qualitative data will be analysed using thematic analysis (with NVivo software). This will combine inductive and deductive approaches and will be conducted collaboratively by a small sub-group of the research team in order to enhance validity.

The Data Monitoring and Safety Committee will oversee analysis at 3 and 12 months for patient safety and at 12 and 24 months for the primary outcome analyses. Given the public health importance of the findings we anticipate disseminating the findings at 12 and 24 month follow-ups as soon as they are available.

(d) Differences in mean costs will be analysed using standard parametric t-tests with the validity of results confirmed using bias-corrected, nonparametric bootstrapping (repeat re-sampling) [50]. Despite the skewed nature of cost data, this approach is recommended to enable inferences to be made about the arithmetic mean [51]. The primary economic analysis will focus on the policy question: MBCT vs. mADM. Cost-effectiveness will be assessed through the calculation of incremental cost-effectiveness ratios (ICER) and will be explored in terms of relapse/recurrence and quality adjusted life years using the EQ-5D measure of health-related quality of life. Uncertainty around the cost and effectiveness estimates will be represented by cost-effectiveness acceptability curves [52].

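### The Design section promises to answer whether mindfulness is the key mechanism, but an MBCT-plus-tapering versus m-ADM contrast can only show results consistent with mediation

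*Protocol article*

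**What the plan says.** The claim is in the Design section of the protocol article: "The trial will answer the explanatory question 'Is an increase in mindfulness skills the key mechanism of change". The sentence goes on to name two routes to the answer, quantitative mediators measured before and after treatment and an embedded qualitative study.

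Secondary research findings defines what is unresolved: "no trials speak to whether MBCT works through its specific hypothesised mechanisms and/or through non-specific cognitive-behavioural, psycho-education and group/therapist support components". It also reports that the cited systematic review sees "the need for randomised controlled trials to compare MBCT with other non-pharmacological approaches". The section on why the trial is needed now gives the lack of mechanism evidence as one of its reasons.

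On the arms, Design says that "the proposed trial compares MBCT plus ADM-tapering with m-ADM for patients with recurrent depression". For the comparator, the m-ADM section says: "The m-ADM relapse/recurrence prevention intervention will be an extension of the ADM treatment that is an inclusion criterion for the study". It adds: "Therefore GPs will be responsible for patients' ADM treatment in line with NICE guidelines".

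For the analysis, item (b) of the explanatory questions says: "Mediational analyses will investigate hypothesised mechanisms of change pre-/post-treatment across the trial arms". It allows several mediators in one model. Process data adds measurement at baseline and one month after MBCT (or the matching time in the other arm), with control for change in symptoms.

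**The concern.** The article sets up a choice between a specific mechanism and a list of non-specific ones, and then promises to settle it. Settling it needs a contrast in which mindfulness training differs while the non-specific components are held alike, or strong assumptions in place of that contrast. The design has no such contrast, and the article does not state the assumptions.

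What is at stake is the reading of a positive mediation result. If group or therapist support both raises mindfulness scores and lowers relapse, a model with arm and mindfulness change can credit mindfulness with an effect that belongs to support. The explanatory question appears in the abstract alongside the policy question, and the abstract's Discussion expects the process studies to yield evidence on which components are effective. Readers would take such a result as resolving the issue that the background raises, while the alternatives listed there remained open.

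**Working it through.** The documents give no figure for this point, so there is none to reproduce. The check is on identification, followed by an illustration.

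**Step 1: components by arm**

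| Component | MBCT arm | m-ADM arm | Where stated |
|---|---|---|---|
| Mindfulness practice | yes | none described | Interventions, MBCT |
| Cognitive-behavioural skills | yes | none described | Interventions, MBCT |
| Psycho-education | yes | none described | Interventions, MBCT |
| Group and therapist contact | yes | GP care only | Interventions, MBCT and m-ADM |
| Antidepressant | invited to taper | continued | ADM tapering; m-ADM |

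Two arms give one randomised contrast, and five rows differ across it. That contrast identifies the effect of the bundle and not of any row. A larger sample narrows the interval for the bundle but does not divide it.

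**Step 2: what the mediation model adds**

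Mindfulness change also varies between patients within an arm, so its association with relapse can be estimated with arm in the model. The components are inseparable only in the between-arm difference. Reading the within-arm association as causal requires that nothing unmeasured drives both mindfulness change and relapse.

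**Step 3: illustration of a failure of that assumption**

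All effect sizes here are assumed, because the documents give none.

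- Sample: 210 × 0.8 = 168 per arm (Table 1 size and attrition).
- Support S exists only in the MBCT arm, with mean 1 and SD 1.
- Mindfulness score M = m·S + noise. Outcome Y = b·S + noise. Both noise SDs are 1, and M has no effect on Y.
- Model: Y regressed on arm and M, with 1,000 replicates.

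The expected false coefficient for M pools the within-arm covariances and variances: (m·b + 0) / ((1 + m²) + 1) = m·b / (2 + m²).

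| m | b | Formula | Simulated mean | M significant at 5%, S unmeasured | M significant at 5%, S in model |
|---|---|---|---|---|---|
| 0.3 | −0.2 | −0.06/2.09 = −0.029 | −0.030 | 9.0% | 4.7% |
| 0.5 | −0.3 | −0.15/2.25 = −0.067 | −0.066 | 23.8% | 4.6% |
| 0.5 | −0.5 | −0.25/2.25 = −0.111 | −0.108 | 51.3% | 4.5% |

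Formula and simulation agree. Measuring support without error and modelling it restores the nominal 5%.

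The size of the false share can be read off as well. The arm effect on M is m and the total effect of arm on Y is b, so the apparent proportion mediated is m × [m·b/(2 + m²)] / b = m²/(2 + m²). That is 0.09/2.09 = 4% for m = 0.3 and 0.25/2.25 = 11% for m = 0.5. In these settings a significance test is misled more easily than an estimate of the share.

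The model is linear and the trial will use time to relapse, so the table shows direction and mechanism. It does not predict error rates for this trial.

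**The case against.** The best defence is that m-ADM is the right comparator for the main question, and that the same background section reports the review finding no trials against an active treatment and suggesting that as the next step. That stands, and nothing here calls for a third arm.

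The article also plans more than a bare mediation test: measurement timed to precede relapse, control for symptom change, several mediators in one model, qualitative accounts, and Cox models that take account of antidepressant use, one of them in the MBCT arm. These deserve credit. None of them creates a contact-matched contrast or removes the need to assume no unmeasured common cause of mindfulness change and relapse. That assumption is needed in mediation analyses generally, so the fault is in the unqualified claim and not in the choice of method.

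The wording is also narrow in extent. Only the Design section promises an answer. The abstract says that the question is asked and will be addressed, and Process data says that it is addressed.

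Three stronger readings are tempting and are not supported:

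- *The trial fails to measure group or therapist support.* The article names no individual process instrument, not even the mindfulness scale. The full protocol may list such measures, so their absence here shows nothing.
- *The mediation analysis is bound to show mediation by mindfulness.* In the illustration it did so in 9% to 51% of trials, depending on assumed effects.
- *Lower antidepressant exposure is itself a strong rival explanation.* The exploratory trial differed by 411.4 − 266.46 = 144.9 days over about 450. Mediators are measured one month after MBCT, while discontinuation is encouraged within six months of the group's end, so much of such a gap would come later. Less medication is also not an obvious cause of fewer relapses on the article's own premise that it prevents them.

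**Conclusion.** The concern holds in a limited form. The Design section claims a property that the two-arm comparison lacks: it cannot tell a mindfulness-specific effect from the non-specific effects that the article lists as the open question. The mediation and qualitative work can support or weaken the mindfulness account, but cannot establish it as the key mechanism.

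The identification point rests only on the arms as described and needs no numerical assumption. How far the mediation estimate might mislead is unknown. The simulated rates and shares depend on assumed effects, a linear outcome, and support that is present in one arm and unmeasured.

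A reader might infer that the explanatory study is worthless or that the comparator is wrong. Neither follows. The primary outcome, the sample size and the randomised policy comparison are untouched.

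**What to change.** In Design, replace the promise with a claim that the comparison supports: the trial tests whether change in mindfulness is consistent with partly mediating the difference between MBCT plus tapering and m-ADM. State there that specific and non-specific components cannot be separated with this comparator. Bring the abstract's Discussion and Process data into line.

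In item (b) of the explanatory questions:

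- State the assumption of no unmeasured confounding between mediator and outcome.
- Add a sensitivity analysis showing how strong an unmeasured common cause of mindfulness change and relapse would have to be to remove the mediated effect.
- Label any analysis of mindfulness change and later relapse within the MBCT arm as associational. Do not adjust it for sessions attended as a stand-in for group contact, because attendance reflects mindfulness training as much as contact and adjustment could remove the effect of interest.

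The cost is a few sentences and one sensitivity analysis on data already planned. The downside is a weaker mechanistic claim.

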### Setting, participants, recruitment and randomization

Four hundred and twenty patients will be recruited through primary care and treated in accessible primary care or community settings. Inclusion and exclusion criteria were refined through the exploratory trial to maximise real world applicability to the population of people in primary care with recurrent depression who are treated with ADM and who are interested in considering a psychological approach to relapse/recurrence prevention. Inclusion criteria are: a diagnosis of recurrent major depressive disorder in full or partial remission according to the DSM-IV, with 3 or more previous major depressive episodes; aged 18 or older; and on a therapeutic dose of ADM in line with the British National Formulary (BNF) and NICE guidance [11]. Currently MBCT is indicated only for more recurrent depression (3 or more episodes) based on the initial trial and its procedural replication [24]. To meet inclusion criteria the participant must have experienced three previous episodes where depression is the primary disorder and not secondary to substance abuse or bereavement. Exclusion criteria are: patients who are currently depressed, co-morbid diagnoses of current substance abuse (patients with previous substance abuse are eligible for inclusion as long as they are in sustained full remission); organic brain damage; current/past psychosis, including bipolar disorder; persistent antisocial behaviour; persistent self-injury requiring clinical management/therapy; and formal concurrent psychotherapy. We include older adults with depression on the basis of the high prevalence of depression in older adults and a promising pilot study of MBCT with this group [29].

The exploratory trial developed a recruitment methodology that proved acceptable and effective [30]. In each of the four localities (Bristol, Exeter, Plymouth/South Devon and North Devon) and five compact 'time slices' that coincide with MBCT group times, research staff will recruit participants meeting inclusion and exclusion criteria, attempting to ensure that baselines assessments occur as closely as possible, normally within one month, to the start of the next MBCT group.

***Randomisation ***will use permuted block randomisation using computer generated quasi-random numbers. Randomisation will be stratified according to recruitment locality (4 sites, enabling a steady flow to treatment groups) and participants' symptomatic status at intake assessment (asymptomatic *vs*. partially symptomatic), using the GRID-Hamilton Rating Scale for Depression GRID-HAMD [31] cut-off of less than eight being asymptomatic and greater than or equal to 8 being partially symptomatic.

Figure 1 summarises the trial Consort diagram.

